**Methods:**

Three communities in southern Malawi begin implementation in randomly-assigned order using a stepped wedge design. Our evaluation sample size of 144 adults and 144 youth per community provides sufficient power to examine primary outcomes of condom use and HIV testing. Prior to any implementation, the first participants in all three communities are recruited and complete the Wave 1 baseline survey. Waves 2–4 surveys occur after each community completes roll-out. Each community follows the model’s three steps. During Prepare, the community develops a plan and trains peer group leaders. During Roll-Out, peer leaders offer the program. During Sustain, the community makes and carries out plans to continue and expand the program and ultimately obtain local funding. We evaluate degree of implementation success (Aim 1) using the community’s benchmark scores (e.g, # of peer groups held). We assess implementation process and factors related to success (Aim 2) using repeated interviews and observations, benchmarks from Aim 1 and fidelity assessments. We assess effectiveness of the peer group intervention when delivered by communities (Aim 3) using multi-level regression models to analyze data from repeated surveys. Finally, we use mixed methods analyses of all data to assess feasibility, acceptability and sustainability (Aim 4).

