## Background

Addressing HIV transmission in low-resource countries in sub-Saharan Africa is essential to meeting the UNAIDS 2030 goal of no new HIV infections [1]. Although new infections continue to decline, there were 1.8 million new infections globally in 2016, and 64% of these occurred in sub-Saharan Africa [2]. Nearly 40% of new infections occur among young people ages 15–24. Scaling-up evidence-based behavior change interventions can help prevent new infections by reducing knowledge gaps and risky sexual behaviors and increasing early testing and treatment.

Our research team developed an evidence-based behavior change intervention for HIV prevention and testing in rural Malawi, an African country hard hit by the HIV epidemic. This 7-session peer group intervention, called *Mzake ndi Mzake* (Friend-to-Friend, *Mzake*), is guided by Bandura’s social-cognitive learning theory [3] that emphasizes building self-efficacy, which has been linked with efficacy in previous meta-analyses and reviews [4–9]. Each session incorporates games and role-plays that rehearse specific steps needed for HIV prevention, such as discussing condom use with a partner. Importantly, the intervention is designed for all reproductive aged individuals regardless of age or gender. Using a quasi-experimental design, we compared a random sample of adults and youth in communities that received *Mzake* and control communities. People in the *Mzake* communities reported significantly more HIV prevention behaviors, including more condom use (Adults, 25% vs. 12%; Youth, 70% vs. 49%) and more HIV tests within the past year (Adults, 18% vs. 10%; Youth, 14% vs. 7%) [10–12].

With efficacy established, this intervention is ready for wider dissemination to other rural communities in Malawi. In the efficacy study, volunteer health workers served as peer leaders and provided training. However, persistent health worker shortages mean that Malawi’s health system does not have the capacity to lead community scale-up because they must meet expanding demands for HIV testing and treatment as well as other health needs.

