### Setting and sample

The study takes place in Phalombe District in southern Malawi. The district has a population of nearly 350,000 [30]. In consultation with District leaders, we identified one sub-district area as the most appropriate place to test the 3-step model. This area is the largest in the district; a third of the district’s population resides there. The leaders in that area selected three communities as sites for implementation.

The sample includes both the implementation partners described above, who share their perspectives on the implementation process (Aim 2), and community members, who participate in the intervention (Aim 1) and its effectiveness evaluation (Aim 3). District level leaders from government, the health sector and traditional leaders collaborate for implementation and are included in qualitative evaluation. Implementation partners in each of the three communities include a coordinating committee that will oversee implementation and the trained peer leaders. Eligibility criteria for implementation partners include being in the designated role and willingness to participate.

The community member participants include adults and youth (ages 13–19) who take part in the 7-session peer group intervention. The first 144 adults and 144 youth in each community participate in both the peer group intervention and the repeated effectiveness surveys. Participants also provide information for the process evaluation during periodic group session observations, focus groups and repeated individual interviews. Eligibility criteria for community participants include residing in the designated community and, for youth, being within the designated age range and having parental permission to participate if under age 18. We subsequently increased the number of youth recruited, because they are more likely to move away over time.

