#### Power analysis, Aim 2 effectiveness

We performed a power analysis for the stepped wedge effectiveness component to determine sample size. Conventional power calculation programs are not able to consider both the intra-class correlation (ICC) for the intervention clusters, and the ICC for repeated measures of individuals over time. Therefore, we performed 1000 simulations using the stepped wedge design, for both continuous outcomes (analyzed using mixed-effects regression) and binary outcome (analyzed using mixed-effects logistic regression) [31, 32]. We conservatively set cluster-level ICC to be 0.10, based on two previous community or classroom studies that found an ICC of 0.05 [33, 34]. Individual-level ICC was set to range from 0.2 to 0.4, as is typical for correlations between repeated measurements of an individual. We set retention rates at 85, 80, and 75% at waves 2 through 4, a conservative estimate given our prior study with 80% retention at 18 months. Expected effect sizes (0.10 to 0.20 for continuous outcomes; odds ratios ranging from 1.2 to 2.2 for dichotomous outcomes) were based on significant outcomes in our previous efficacy study [10, 11] or, for comprehensive HIV knowledge and sexually transmitted infection (STI) prevalence, a 2010 national survey [35]. With 80% statistical power, the sample of 432 persons (youth or adults) with retention rates of 75% at the last wave, supported a minimum detectable effect size of 0.13 for continuous outcome variables, and a minimum detectable odds ratio of size 1.36. Thus, we have sufficient power to detect all expected intervention effects for outcome variables for adults and youth separately.

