#### Implementation at 3 sites

We test the 3-Step Model in the 3 sites sequentially, with the order of introduction at each site randomly assigned during a public meeting. The same sequence of implementation steps and activities occurs at all sites.

During the *Prepare* step (2 months), community leaders are oriented to the program and form a site coordinating committee comprised of respected adults active in community affairs. The committee is oriented to the 3-Step Model and *Mzake.* They learn about the benchmarks which they use to develop a plan and evaluate progress every 6 months (Table 1). After making a community implementation plan, they recruit volunteers to become peer leaders. The volunteers are trained to deliver *Mzake,* maintain group records and complete a brief self-evaluation of fidelity. *The primary capacities built during this period are conceptual understanding of the* 3-Step Model *and Mzake; planning and coordination for the coordinating committee and peer group leadership skills for peer leaders.*

During *Roll-Out* (8 months), *Mzake* is introduced to community members at village meetings and those who are interested sign up to be in the peer groups and complete informed consent. The first 144 participants must also agree to complete the repeated effectiveness surveys. Peer leaders conduct the first round of 12 groups with adults, then reflect on their experiences with the coordinating committee and make any modifications. Because talking about sexuality with youth is a sensitive topic in Malawi, the leaders obtain experience and confidence with adult groups and then the same peer leaders offer 12 groups with youth. During both adult and youth groups, the research team rates fidelity and provides supportive coaching for each pair of leaders during at least one early session and one later session, rating fidelity and providing coaching to the leaders. After these initial peer groups are completed, the peer leaders and committee will meet to reflect on lessons learned and prepare for future implementation. The lessons learned from both rounds of groups will be shared with implementation partners and iteratively used to modify the 3-Step Model. *The primary capacities built during this period are: experience in using the* 3-Step Model *and offering Mzake, practical logistics for local implementation and completing the benchmarks self-evaluation for committee members.*

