#### Aim 3 (effectiveness analysis)

The effectiveness of the *Mzake* intervention when offered by communities is determined by survey data and STI symptom interviews with a nurse at Waves 1–4. We will complete a CONSORT diagram showing recruitment, retention and loss to follow-up at each wave. We then examine significant factors associated with lost to follow-up. Identified attrition factors will be controlled in later analyses.

To evaluate the effectiveness of the intervention in improving HIV-related outcomes, we will use multi-level mixed-effects regression (for continuous outcomes) and logistic regression (for dichotomous variables) models [51]. These methods allow us to take into account time of implementation as well as lack of independence among repeated measurements and members of the same peer group. The hierarchical structure of the data is conceptualized as repeated outcome measures (level 1), nested within individuals (level 2) and nested within peer groups (level 3). Random individual and peer group effects will account for correlations between repeated measurements and between individuals from the same peer group. Intervention condition will be a time-varying covariate that reflects the stepped-wedge design in which individuals receive intervention at different stage of the study. Site and demographic factors (both individual level and community level) will be treated as fixed-effects covariates to account for differences. Time trend interactions for intervention and imporant factors will be tested to identify differential effects over time. Youth and adult data will be analyzed both together and separately. Model selections for the number of random effects and the variance-covariance structures for the outcome variables will be performed using likelihood ratio tests. Backward selection will be employed for the fixed effects. *Aim 3 analysis identifies effectiveness overall and by site.*

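### Backward selection over all fixed effects, with no protected wave term, can remove the main confounder from the stepped-wedge model and pass a secular trend off as an intervention effect

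*Protocol article*

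**What the plan says.** The section Aim 3 (effectiveness analysis) sets out multi-level linear and logistic models with random effects for individual and peer group. Intervention enters as a time-varying covariate. On the other fixed effects it says: "Site and demographic factors (both individual level and community level) will be treated as fixed-effects covariates to account for differences". Interactions with a time trend are to be tested, and factors found to predict loss to follow-up are to be controlled. The fixed-effects rule is one sentence: "Backward selection will be employed for the fixed effects". It names no exempt term and no removal threshold. No main effect of wave or period is listed anywhere in the article.

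The design is given in the Abstract: "Three communities in southern Malawi begin implementation in randomly-assigned order using a stepped wedge design", and "Waves 2–4 surveys occur after each community completes roll-out". Under Setting and sample: "The first 144 adults and 144 youth in each community participate in both the peer group intervention and the repeated effectiveness surveys".

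**The concern.** In a stepped wedge, exposure rises with calendar time by construction. Only adjustment for time separates the programme from whatever else changes over the same years. The collinearity that makes the adjustment necessary also weakens the test of the wave term, so selection by significance tends to remove wave when it is needed.

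Some change over time is plausible here. Participants aged 13 to 19 at entry grow older over several waves, and their sexual activity, condom use and testing may shift with age alone. The Background also says of health workers that "they must meet expanding demands for HIV testing and treatment as well as other health needs", and an HIV test in the past year is a primary outcome. If wave is dropped, part of such a change is reported as effectiveness on the primary outcomes.

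**Working it through.** **Inputs from the article.** Three sites; 144 adults and 144 youth per site, so 3 × 144 = 432 per age group; four waves; retention 85%, 80% and 75% at Waves 2 to 4; individual ICC 0.2 to 0.4. For clustering, "We conservatively set cluster-level ICC to be 0.10". For peer groups, "Peer leaders conduct the first round of 12 groups with adults", taken as 144/12 = 12 persons per group.

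**Assumptions, not in the article.** Two-sided alpha 0.05; removal at p>0.05; a linear secular trend whose size is varied; a continuous outcome with SD 1.

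**1. The plan's own figure.** MDE = (1.96 + 0.84) × SE of the intervention term.
- Without a time term, the layout gives an MDE of 0.115 to 0.144 over the stated ICC range. Power at 0.13 is 79.5-79.7% for an individual ICC of 0.35 read as total, or 0.25-0.30 read as additional to the cluster ICC. The stated 0.13 is reproduced.
- With a linear or categorical wave term, every variant tried gives 0.198 to 0.250.

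**2. Bias once wave is dropped.** Take complete data with site fixed. Exposure by wave is (0,1,1,1), (0,0,1,1) and (0,0,0,1), and the trend is δ × (0,1,2,3).
- Within-site cross-products of exposure and time: 1.5 + 2 + 1.5 = 5.
- Within-site sums of squares of exposure: 0.75 + 1 + 0.75 = 2.5.
- False effect = 5δ/2.5 = 2δ, which is 2/3 of the total trend 3δ.

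The planned dropout leaves this essentially unchanged. A trend of 0.05 SD per wave gives a false effect of 0.10 SD. A total change of 0.20 SD gives 0.133, about the stated detectable effect.

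**3. Precision lost by keeping wave.** After adjusting for both site and wave, the exposure sum of squares falls from 2.5 to 0.306 + 0.222 + 0.306 = 0.833. The SE ratio is √(2.5/0.833) = √3 = 1.73.

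**4. Type I error after selection.** Simulation with 200,000 draws, no true effect, site forced in, wave as a three-indicator block, planned retention and individual ICC 0.3:

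| Trend (SD per wave) | Every other term removable, largest p out first | Intervention protected | Wave forced in |
|---|---|---|---|
| 0 | 5% | 6% | 5% |
| 0.02 | 9% | 14% | 5% |
| 0.03 | 13% | 23% | 5% |
| 0.05 | 20% | 45% | 5% |
| 0.08 | 17% | 50% | 5% |

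With intervention protected, wave is dropped in 90% of trials at 0.03 SD per wave and in 80% at 0.05. Over individual ICC 0.2 to 0.4 and trends of 0.02 to 0.08, the two selection columns span about 9-20% and 13-53%.

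Under literal elimination the error peaks near 20% and then declines. From 0.05 SD per wave upward, intervention itself is the first term removed in 71-88% of trials.

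**5. Deleting site while wave stays.** For a gap between the first and third site of 0.1 to 0.3 SD, type I error is 5.5-8.5%.

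**The case against.** The strongest reply is that the sentence is shorthand. The same section says its methods allow for implementation timing, includes site to adjust for differences, promises control of attrition factors and intends results overall and by site. That suggests intervention and site stay in, and that selection is meant for covariates and interactions. Forced terms and thresholds are also details a condensed article may leave to a fuller document. This softens the point but does not remove it: the article states a rule, the rule exempts nothing, and wave is not among the named terms. If wave was never meant to be in the model, the bias in step 2 applies without any selection.

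Other limits stand. The article gives no secular trend and no removal threshold. The remark on growing demand concerns health-system workload; it is not a measured trend in these outcomes. With no trend the inflation is negligible.

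A reader might go further in four ways that the documents do not support:
- **That the false-positive rate is near 50%.** That needs intervention to be protected while wave is not, and a trend near 0.05 to 0.08 SD per wave. Under literal elimination the peak is about 20%.
- **That losing site also turns secular change into an effect.** It lets baseline differences between sites leak in, with far less harm (step 5).
- **That no community-level covariate can be fitted beside site.** This is true only of covariates constant over time, which are aliased with the two site indicators. Values that change by wave vary over 3 × 4 = 12 site-by-wave cells.
- **That the power simulation left out time.** The match in step 1 points that way, but the fitted model is not described.

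**Conclusion.** The point holds for wave. As written, the rule can delete the main confounder of a stepped-wedge comparison, and it tends to do so when a moderate trend exists. The false effect is then two-thirds of the Wave 1 to 4 trend, whatever the sample size.

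The error rates in step 4 are conditional on the assumed trend, the p>0.05 threshold and a continuous outcome. Which of the two selection columns applies depends on whether intervention is exempt, and the article does not say. Condom use and HIV testing, the primary outcomes named in the Abstract, are analysed at least partly as binary variables. The mechanism carries over, but the percentages were not simulated for them. The site and community-covariate issues are minor beside this.

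**What to change.** Replace the selection sentence with wording such as:

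> Intervention, wave (three indicators) and site (two indicators) are forced into every Aim 3 model. Prespecified individual-level covariates and identified attrition factors are included and are not removed by significance. Community-level covariates that are constant over time are not fitted beside site, because they are aliased with it.

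No new data are needed, but the change costs more than wording. The intervention standard error rises about 1.73-fold, and the minimum detectable effect becomes about 0.20-0.25 instead of about 0.12-0.14. Power at 0.13 falls to about 31-45%. At an assumed 25% base rate, the approximate detectable odds ratio moves from 1.30-1.40 to 1.58-1.78.

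The power section should therefore be recomputed with wave in the model, and its 0.13 and 1.36 restated. Its claim of sufficient power for all expected effects needs the same revision: a detectable effect of 0.20-0.25 lies at or above the top of the expected 0.10 to 0.20 range.

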#### Aim 4 (integrated 3-Step Model analysis)

The 3-Step Model’s feasibility, acceptability, effectiveness and sustainability for implementation by communities is evaluated by integrating data and analysis results from Aims 1–3. Our analysis focuses primarily on the relationships among the extent and patterns of implementation identified in Aim 2 and whether implementation variations are related to effectiveness and implementation success and sustainability. This mixed-methods analysis can be conceptualized as a comparative case study with 3 cases [49, 52]. We use the same mixed-methods approach and methods described above. We first develop within and across case matrices to identify patterns and relationships, and then examine detailed case summaries to understand the complex context that surrounds similarities and differences. For example, if only 2 sites were able to use the 3-Step Model with fidelity to sustain implementation to the end of the study period and both had high effectiveness, a close examination of the less successful site should identify potentially important differences and point to aspects of the 3-Step Model that need improvement. *Aim 4 analyses will link the community implementation process and patterns of using the 3-Step Model with the effectiveness evaluation results and sustaining of the intervention. Lessons learned from these analyses will tell us how well communities were able to use this 3-Step Model and help identify contextual factors that appear to enhance or inhibit sustainability.*

## Discussion

This study will test whether community members can take ownership and successfully scale-up implementation of an evidence-based intervention. While many community studies use a participatory approach, there are few published accounts where communities organize and manage implementation. Our hybrid design enables us to simultaneously examine facilitators and challenges affecting the community implementation process and program effectiveness when implemented by community members under real-world conditions.

Two of the three communities have already begun rolling-out the intervention. Leaders have established a coordinating structure and a plan for spreading the intervention in their villages. Our district-level partners have made the contributions they agreed upon, although communities have not yet reached the point of seeking additional local funding for long-term sustainability.

Along the way, we have encountered several challenges. Initiating a complex project in two linked but geographically distant universities is never simple. Executing a subcontract and transferring funds, and then completing local hiring, setting up an office in the community and team training took many months. Consequently, although we continued planning with district and community leaders, project activities at the community level were delayed. These delays were particularly frustrating for community leaders and members, who had been waiting from the time we met with them as we developed our NIH proposal. Keeping community partners engaged from initial project planning through funding and then project set-up is a major challenge, yet bringing them into early stages of project development is an essential part of a participatory approach. We attempted to manage this through frequent contacts and transparency about delays, but this issue remains problematic in participatory research and university-community collaboration.

We also needed to make two modifications in the protocol during early implementation. As described above, shortly after the project began, new data identified that the non-invasive rapid STI measures that had been deemed appropriate for community use had unacceptably low reliability. Therefore, we transitioned to an STI symptoms interview by a nurse. The other change was the addition of a pilot with youth. We initially planned to pilot the program only with adults, but after working with peer group leaders we realized that they lacked confidence about offering *Mzake* to youth. Therefore, we conducted a pilot with youth, which gave the peer group leaders confidence and a better understanding of the need to discuss sexuality issues with youth openly. Lessons learned in the pilot also led our team to create a separate session guide with age-appropriate content and role-play scenarios with more participants to enhance engagement with youth.

This study provides a new approach for scaling-up effective interventions to reduce new HIV infections and will have a major impact on implementation science, especially for community-led implementation. Community-wide implementation of an efficacious intervention has high potential to change sexual risk and HIV testing behaviors, and thus reduce new HIV infections, without imposing new burdens on the health system. The 3-Step Community Implementation Model fills an important gap in implementation science. Moreover, the model is potentially generalizable to community scale-up for a wide variety of evidence-based health interventions. Lessons learned regarding implementation similarities and differences across three different communities and effective strategies to support community scale-up will advance implementation science.

